### Study 2: qualitative study

#### Design

This study aims to gain insight into the implementation process of YIM. To do so, we will conduct focus group interviews with YIM-trained Halt professionals during regularly scheduled supervision meetings. We will first conduct a large focus group, followed by three smaller focus groups. The large focus group aims to gain an in-depth understanding of the implementation of YIM in a specific youth case, while the small focus groups aim to gain insight into boosters and barriers in the implementation process of YIM at Halt. If necessary, we will conduct additional focus groups or individual interviews (i.e., significant variations exist between focus groups).

#### Study sample, recruitment, and data collection

At Halt, 36 professionals are trained in YIM, of which 31 will recruit data for our trial. We will approach YIM-trained Halt professionals during regularly scheduled supervision meetings. All YIM-trained Halt professionals who want to participate in the study will participate in the large focus group, followed by a smaller focus group consisting of 6 to 9 participants (Finch et al., 2014). If individual interviews or additional focus groups need to be conducted, researchers will adopt similar recruitment strategies or approach Halt professionals for individual interviews.

#### Materials

We will develop a discussion format for both types of focus groups (Finch et al., 2014). Based on observations and literature, the format will contain questions within three domains of the Consolidated Framework of Implementation Research (CFIR): the innovation domain (i.e., characteristics of the innovation being implemented: YIM), the individuals’ domain (i.e., characteristics of individuals receiving the innovation: youth and caregivers, and characteristics of individuals delivering the innovation: Halt professionals) and the inner setting domain (i.e., characteristics of the setting in which the innovation is being implemented: Halt) (Damschroder et al., 2009, 2022; Fleuren et al., 2014). For example, “What aspects do you find easy (or difficult) in the implementation of YIM?” or “How do you experience the organisational support to implement YIM?”.

#### Procedure

Professionals will be informed about the qualitative study and must consent if they want to participate. Each participant will follow the large focus group, followed by a smaller one. In the large focus group, we will recreate a *reflecting team* model (Van Dam, 2007; Chang, 2010): in the inner circle, participants will engage in structured discussion about a Halt professional’s prior youth case (*N* = 6–9), and in the outer circle, four smaller circles (*N* = 3–5) will observe the discussion through a specific perspective: (1) the youth; (2) caregivers or YIMs; (3) Halt professional; or (4) Halt. Afterwards, the different perspectives will be discussed in plenary, and all participants will be encouraged to share their thoughts and perspectives. In the smaller focus groups, structured discussions with Halt professionals will be activated via *think-pair-share* techniques (Lyman, 1981). First, participants will be instructed to *think* about the posed question; second, they will be asked to discuss this question in *pairs* and to write down their answers; and third, the pairs will be asked to *share* their findings in the group, after which a discussion will be initiated. This technique encourages individual participation, makes discussions more productive, and improves the quality of the responses (Kagan, 1994). The researchers will collect the *pair* forms, and participants will be thanked and asked whether they have any additional thoughts to share.

#### Data analyses

Focus groups (and possible individual interviews) will be recorded, and these audio files will be transcribed. To identify patterns of themes in the data, we will follow a multi-step thematic analysis approach (Braun & Clarke, 2006). We will perform the six steps of the approach: familiarise with the data, generate initial codes, search for themes, review the themes, define and name the themes, and report on the identified themes. We will use inductive coding strategies for the initial codes, after which we will perform deductive coding strategies based on the CFIR (Damschroder et al., 2009, 2022).

## Discussion

With this study on YIM, a new examination is initiated in the field of youth mentoring for delinquent behaviour. Research on YIM remains limited; thus, we aim to contribute to the further understanding of the effectiveness of YIM as a selective prevention strategy for juvenile delinquency. To do so, we will perform a quasi-experimental trial simultaneously targeting youth resilience and delinquency outcomes and a qualitative study in which professionals will evaluate their experiences with implementing YIM. Moreover, examining how and for whom the YIM works may help to inform a tailored approach when introducing YIM in the field of juvenile delinquency.

The current study has three main strengths. First, we will examine the effectiveness and not the efficacy of YIM. The interventions (i.e., CAU and CAU plus YIM) are implemented under real-life circumstances, allowing us to study the performance of YIM in daily practice rather than the performance under ideal and controlled circumstances (Singal et al., 2014). Thus, the study has high ecological validity (Andrade, 2018). Second, the study is designed in co-creation with Halt professionals, policy officers and management. Real-life circumstances were the starting point of this co-created study: “How can we integrate the study into professionals’ regular working activities?”. Joint-decision making has contributed to the seamless integration of the study into professionals’ working activities and increased their involvement in and support for the study. Third, the study will focus on both resilience and delinquency outcomes. Even though we will examine whether YIM is effective as a selective prevention strategy for juvenile delinquency, we will also focus on youth resilience factors in delinquent youth. By including outcomes relevant to positive youth development, we consider adolescents’ developmental trajectories. By strengthening the social network, YIM might build resilience (Fergus & Zimmerman, 2005; Seigle et al., 2014; Stagner & Lansing, 2009; Ward & Stewart, 2003; Zimmerman, 2013) and, in turn, desistance against juvenile delinquency. Therefore, it is crucial to include these measurements pertinent to youth development.

It is also crucial to mention three potential challenges. First, allocating youths to either condition (i.e., to a non-YIM-trained or YIM-trained professional) is non-random. Random allocation is impossible because Halt’s distribution office considers professionals’ workload. This might lead to an unequal division of youth cases over conditions and, thus, less comparable conditions. Differences between conditions could then possibly be explained by confounding factors instead of the effects of YIM, such as differences in the severity of the youth case (Flannelly et al., 2018). To ensure comparable conditions, we will match professionals in the CAU plus YIM condition within each region to professionals in the CAU condition. Nevertheless, we must be cautious of drawing causal inferences. We will also address other confounding factors between conditions, such as differences in the number of sessions or types of activities. Second, baseline and post-test measurements will occur without the knowledge of the implementation level of YIM in the CAU plus YIM condition. We will assess three levels of implementation steps taken by a professional: (1) the YIM question was asked, (2) steps were taken to support youth in identifying and nominating a YIM, and (3) a YIM was positioned in an official meeting. External factors can influence these steps, such as a youth not being able to identify or nominate a YIM. If this is the case, it is impossible to position a YIM. We will, however, instruct professionals to explain and motivate YIM in all youth cases, possibly leading to the positioning of a YIM. Overall, we expect that all cases will at least have the second level of implementation. However, due to the natural course of YIM, we cannot rule out natural variation in the level of implementation. Because this might impact the findings, we will consider these implementation levels in our analyses. Moreover, these implementation levels will allow us to explore whether different elements of YIM affect the approach’s effectiveness. Third, all participants will voluntarily sign up for the study, potentially leading to a selective pool of more intrinsically motivated participants. Even though Halt has a broad population, with varying degrees of problems and different types and severity of offences and crimes, the registered group might not entirely represent the Halt population. Potentially, youth with more severe problems might be missed. This would, however, apply to both conditions – if this were to be the case. Hence, to appeal to the entire population at Halt, we will offer a monetary contribution per completed questionnaire and the chance to win the grand prize, namely AirPods. Fourth, a challenge in the focus group interviews is that being in a group, people might not feel comfortable enough to share their true perspectives and opinions on working with the innovation. Moreover, some individuals could be more dominant in the conversation than others, which might discourage some individuals from actively participating. To encourage active participation and a comfortable environment, we will perform *think-pair-share* techniques (Kagan, 1994; Lyman, 1981) in a neutral environment without the involvement of YIM and Halt management.

Halt’s population consists of 15,000 juvenile minors each year. Including a representative population of Halt allows for studying how and for whom YIM might work. This knowledge would benefit (Halt) professionals in decision-making on how and when to implement YIM. At the same time, youths who benefit from the approach can be specifically targeted, leading to a tailored approach. Suppose YIM is an effective addition to Halt’s short-term intervention. In that case, YIM can be further implemented within their intervention and potentially more widely within the juvenile justice system, such as juvenile detention centres, even outside the Netherlands. Insight into factors that facilitate or prevent YIM implementation yields specific strategies that impact these boosters or negate these barriers. These challenges and strategies can be considered and adopted by others who aim to implement YIM or a new intervention embedded within an organisation. Overall, this study will contribute to knowledge on whether YIM is a suitable informal mentoring approach for youth within the juvenile delinquency field. Moreover, information on which program elements of YIM work can further strengthen informal mentoring approaches.

This study will investigate the effectiveness of YIM for juvenile delinquents. Subsequently, this study will be able to answer questions considering the working mechanisms and possible boosters and barriers experienced in implementation processes. In conclusion, we will contribute to a further understanding of informal mentoring approaches as a selective prevention strategy within the juvenile delinquency field.

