#### Materials

Our primary outcome, with which we will assess the main intervention effect of YIM on perceived social support and social resourcefulness, will be measured with the Berlin Social Support Scales (BSSS), respectively the subscales ‘Perceived Social Support’ and ‘Support Seeking’ (Schwarzer & Schulz, 2003). All youth and caregiver(s)’ outcomes and measurement points are depicted in Table 1. In Table 2, an overview of measures administered to Halt professionals is presented.

**Table 1 Tab1:** Overview of Youth and Caregiver(s) Measurements

Concepts		Measurement	Informants	# of items	Baseline	Post-test	Follow-up
Demographic factors		Demographics	Y	18–21	*****		
Offense and referral information		Halt’s registration system	HP	-	*****		
Halt intervention characteristics		Halt’s registration system	HP	-	*****		
YIM characteristics		Halt’s registration system	HP	-		*****	
Dynamic risk factors		Halt-SI	HP	-	*****		
Psychosocial problems		Halt-SI SDQ	HP Y	- 20	***** *****		
Prosocial behaviour		SDQ	Y	5	*****	*****	*****

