#### Conditions

**Care as Usual (CAU) condition.** Participants (*N* = 150) will follow the regular Halt intervention implemented by non-YIM-trained Halt professionals, also referred to as *Care as Usual.* Aside from inviting youth to participate, professionals are instructed to follow their regular working activities. During the initial meeting, the content and duration of the Halt intervention (in hours and the number of meetings) are determined by a compulsory screening and risk assessment (i.e., Halt-SI) and the nature of the offence. Tailored to the youths’ needs, the professional then selects activities from five different modules: (1) reflection on one’s behaviour, (2) parental involvement, (3) social skills training, (4) victim-offender reconciliation, and (5) future opportunities. For example, activities in the module ‘social skills training’ are ‘modeling’ and ‘dealing with peer pressure’. It is important to note that victim-offender reconciliation is compulsory for all youth (e.g., writing an apology letter to the victim or providing restitution). After selecting activities, the professional draws up an official contract with agreements on the course of the intervention—signed by the youth. The youth then proceeds to fulfil the activities selected by the professional. Some activities can be done at home, such as writing an apology letter, while others are practised during an intervention meeting with a professional, such as social skills training. Importantly, professionals discuss the completion of each activity with the youth. During the closing meeting, the intervention is completed positively if the youth has complied with all agreements made at the start of the trajectory (Wolthuis & Stentoumi, 2023). If deemed necessary, youth are referred to formal support. The aim is to complete CAU within 100 days. The number of meetings with the professional can vary from one to six, with a minimum intensity of 1 h and a maximum intensity of 20 h. On average, youths follow three meetings: an initial meeting, an intervention meeting, and a closing meeting. The initial meeting is in person, while other meetings can be in person or online. Eighty-five per cent of caregivers are present during the initial and closing meetings and provide support where necessary.

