**CAU plus YIM condition.** Participants (*N* = 150) will follow the regular Halt intervention described above in combination with YIM, which can be selected as an activity from the module ‘future opportunities’. If selected, it replaces other Halt activities. During the initial meeting of Halt, professionals in this condition help all youth to identify a mentor by asking the YIM question (i.e., “Who in your environment (an adult, aside from your caregiver(s)) can you turn to if necessary?”). If at least three meetings are necessary, professionals explain what YIM entails and support youth by using the network or YIM assignment, which helps to gain insight into the youth’s network. A positive or negative reaction of the youth can follow. A minimum of four (online) meetings are integrated into Halt’s regular working activities if the youth has identified and nominated a YIM. The first meeting is a conversation between the Halt professional and the YIM. They discuss the reaction of the YIM to being asked by the youth, the help needed by the youth, the YIM’s expectations for the trajectory and the role of the professional. The professional explains that the mentor and the youth have the autonomy to form the trajectory to the youth’s needs and the mentor’s possibilities. The mentor will function as a confidant and ally to the youth in various situations (e.g., listening to the youth or supporting the youth with schoolwork). Mentors are not trained because, in YIM, it is believed that the YIM has all the knowledge and tools to support the youth. The professional has a facilitating role, meaning that they initiate the mentoring trajectory and, if necessary, can be reached for support on the YIM’s initiative. The second meeting officially positions the “YIM”. The youth, caregivers, YIM, and professional discuss each other’s expectations, formulate goals, agree on the support frequency, and plan the evaluation meeting. Thus, the type and frequency of support may vary over youth cases. The mentor can partner with caregiver(s) and professionals by making agreements regarding specific goals (e.g., ensuring a youth goes to school in the case of extreme school absenteeism). Again, the professional takes a facilitating and supportive role. In the third meeting, the professional and the YIM have interim contact to discuss the trajectory and if they can proceed with the evaluation meeting. If this is not the case, they plan another interim contact moment. However, if this is the case, the fourth meeting is a joint evaluative meeting during which the youth, caregivers, YIM, and professional evaluate the goals and agreements made at the start of the trajectory. They also discuss how to proceed and whether it is possible to end Halt’s involvement. If so, this also functions as a closing meeting. Similar to CAU, the completion of Halt is evaluated by the Halt professional, while the completion of YIM is evaluated by all parties (i.e., youth, caregiver(s), YIM and professional). Moreover, the aim is to complete CAU plus YIM within 100 days. Importantly, because YIM meetings are integrated into Halt’s regular working procedures and replace other Halt activities, we expect the same number of meetings between the youth and the professional. However, extra meetings between the youth and their YIM are not uncommon, and the YIM often remains involved after Halt’s involvement has ended.

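### Activity type and session count are named as confounders to be addressed, but both are fixed after allocation and activity type is partly the treatment itself

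*Protocol article*

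**What the plan says.** - **Discussion, first challenge.** After acknowledging non-random allocation, the article states: "We will also address other confounding factors between conditions, such as differences in the number of sessions or types of activities". It does not say by what method.
- **Conditions, CAU.** "During the initial meeting, the content and duration of the Halt intervention (in hours and the number of meetings) are determined" by the Halt-SI screening and the nature of the offence; the professional then selects the activities. "On average, youths follow three meetings: an initial meeting, an intervention meeting, and a closing meeting".
- **Conditions, CAU plus YIM.** YIM is an option "which can be selected as an activity from the module" on future opportunities. "If selected, it replaces other Halt activities". "A minimum of four (online) meetings are integrated into Halt’s regular working activities if the youth has identified and nominated a YIM", yet "we expect the same number of meetings between the youth and the professional".
- **Materials, Table 1.** The row "Halt intervention characteristics" is marked in the baseline column. Data collection and procedure gives number of meetings and type of crime as examples of these characteristics.
- **Data analyses.** The effect model has the baseline outcome and condition. Conditions are compared on an open list of characteristics, and propensity score matching follows if differences are found. Analysis is by assigned condition, whatever was received.
- **The present study.** Halt intervention characteristics are also listed among the moderators.

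**The concern.** A confounder has to precede the treatment or at least be unaffected by it. What is delivered after a youth has been allocated to a professional does not meet that condition if the professional's condition shapes it. For activity type the article itself says that it does.

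The label matters because the plan has a route by which it could reach the main estimate. Differences between conditions trigger propensity score matching, the list of compared characteristics is open, and Table 1 files the delivery data under baseline. Activity mix should differ between arms by design. A balance check that included it would therefore be likely to trigger matching, and matching would then favour YIM-arm youths who received no YIM and CAU youths with unusual programmes. The result would no longer answer whether CAU plus YIM differs from CAU, and it would sit badly with analysis by assigned condition.

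**Working it through.** The plan gives no figure for the relation between condition and sessions or activities, so there is no stated number to reproduce. The timing and content argument rests on the text alone; the sizes below rest on stated assumptions.

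**1. Timing.** The preliminary conversation, held by the recruiting (allocated) professional, comes first. The baseline questionnaire is to be completed before the initial meeting. Content, hours and number of meetings are determined at the initial meeting. Both variables therefore follow allocation and baseline.

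**2. Activities.** YIM is offered only by YIM-trained professionals, it is itself an activity, and it displaces others. Activity type is thus partly the treatment contrast.

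**3. Sessions.** The CAU average of three meetings consists of initial, intervention and closing. Of the four YIM meetings, the first and third involve the professional and the YIM, while the second and fourth include the youth; the fourth may double as the closing meeting. Taking the initial meeting as separate from these four:
- meetings between youth and professional: 1 + 2 = 3, against 3 on average in CAU;
- all meetings held by the professional: at least 1 + 4 = 5, against 3 on average in CAU.

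The CAU average covers programmes of one to six meetings, whereas the trial keeps only youths with at least three, so even this is not a like-for-like comparison. Whether YIM changes session count depends on which count is registered, and the article does not say.

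**4. Direction of bias (assumed model).** Let T be condition, S unmeasured severity (balanced between arms here, so that all bias comes from the adjustment) and M the delivery variable:
- M = aT + sS + error
- Y = (τ − ab)T + bM − 0.3S + error

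S and both errors have unit variance, and the total effect τ is 0.21, the value cited under Power Analysis, used only as a yardstick. Simulated means are from 2,000 runs at 150 per arm.
- M helpful and raised by YIM (a = 1, b = 0.1, s = 0): adjusted effect τ − ab = 0.21 − 0.10 = 0.11 (simulated 0.10).
- M helpful and displaced by YIM (a = −1, b = 0.1, s = 0): 0.21 + 0.10 = 0.31 (simulated 0.31).
- M a severity marker with no effect of its own (b = 0, s = 0.5): the within-arm slope is −0.3 × 0.5 / (0.25 + 1) = −0.12, so the adjusted effect is 0.21 + 0.12a. This is 0.09 if YIM lowers M and 0.33 if YIM raises it (simulated 0.09 and 0.33).
- M unchanged by YIM (a = 0): 0.21 (simulated 0.21).

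The unadjusted estimate is 0.21 throughout, with SE 0.12. Where YIM changes M, the adjusted SE is 0.13 to 0.135.

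**5. Precision (assumed ranges).** The SE ratio, adjusted over unadjusted, is √[(1 − r²)/(1 − ρ²)]. Here ρ is the correlation of M with condition and r² the share of residual outcome variance that M explains.
- ρ = 0.3: 1.05, 0.99 and 0.88 for r² = 0, 0.10 and 0.30.
- ρ = 0.5: 1.15, 1.10 and 0.97.
- ρ = 0.7: 1.40, 1.33 and 1.17.

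For a yes/no variable such as use of the future opportunities module, ρ = (pA − pB) × 0.5 / √[p̄(1 − p̄)]. With r² = 0:
- 80% v 40%: ρ² = 0.17, SE +10%.
- 63% v 10%: ρ² = 0.30, SE +20%.
- 80% v 10%: ρ² = 0.49, SE +41%.
- 86% v 5%: ρ² = 0.66, SE +72%.

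The 63–86% is the article's range for youths able to name a natural mentor, borrowed here as a stand-in for module use. The 80% and all the CAU percentages are assumptions.

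**The case against.** The sentence stands in the Discussion and says that the factors will be addressed, not adjusted for. The effect model in Data analyses contains neither variable, the examples given for the balance comparison are of another kind, and the moderator role could be what is meant. This stands: a reader might infer that the plan commits to covariate adjustment, and it does not. What remains is that treatment components are called confounders in a paragraph on comparability, which makes adjustment or matching a natural reading.

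Content and duration also follow the Halt-SI and the offence, so they partly mark pre-existing severity, a real worry without randomisation. This stands too, and it rules out saying that these variables carry no information on confounding. It argues for adjusting for severity directly rather than through what was delivered.

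For sessions, the article expects equal youth-professional meetings. A reader might infer from the four-against-three figures that YIM raises the session count; step 3 of the working shows that the text does not establish this.

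Finally, a reader might infer that adjustment would necessarily shrink the effect and inflate its standard error. Neither is supported. Because YIM displaces other activities, adjustment can overstate the effect, and a prognostic covariate can offset the loss of precision.

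**Conclusion.** The concern holds in a limited form. Calling activity type a confounder is wrong on the article's own description, because it is fixed after allocation and YIM is one of the activities. Conditioning on it would change the estimand from the total effect of CAU plus YIM against CAU. For session count, only the post-allocation timing is certain; whether YIM changes it turns on statements that must be reconciled.

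The bias has no fixed direction. In the illustration it reaches 0.10 to 0.12 on a true effect of 0.21 (0.10/0.21 = 48%; 0.12/0.21 = 57%), but this rests on assumed path strengths and on the variables actually being used for adjustment or matching. The precision cost ranges from a gain (ratio 0.88) to a clear loss (ratio 1.72) over the assumed inputs, so no single figure should be quoted as the plan's.

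**What to change.** - **Discussion:** remove number of sessions and types of activities from the confounding factors. State that they stay out of the main model, out of the balance check that triggers matching, and out of the propensity score.
- **Severity:** control it with characteristics that condition cannot affect: offence and referral information, Halt-SI risk items, baseline psychosocial problems and the baseline outcome. The Halt-SI is completed at the initial meeting, so a rule admitting only variables recorded before that meeting would wrongly drop it. Keeping it assumes that the rating does not depend on whether the professional is YIM-trained, and the text should say so.
- **Delivery data:** report sessions, hours and activities by arm. Label any analysis that conditions on them as secondary and mediation-type, and say how this relates to their listed role as moderators.
- **Table 1:** mark the Halt intervention characteristics as post-allocation, keeping type of crime with the offence information.
- **Conditions:** reconcile the expectation of equal meetings with the minimum of four and the CAU average of three, and state which meetings count as sessions.

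The cost is wording only; no new data are needed.
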